### Data analysis

The data management and analysis department (HCL) will carry out the whole process at the end of the intervention phase: data extraction and analysis will be performed by two different persons. The data manager will prepare the dataset and ensure to blind the arms of the study, so that the statistician in charge of the analysis has no clues about the arms. Analyses will only be unblinded after results obtention for final interpretation.

We will use a difference in difference (DID) approach successively to assess intervention impacts on the evolution of adverse event rates. We will compare the evolution of adverse event rates in the two intervention arms and in the control arm between the pre-measurement 1-year period and the 2-year intervention period. In case of significant differences among the arms, we may consider data collected 1 year after the end of the intervention (follow-up measurement).

Analyses will follow the intention-to-treat approach, including data from all patient’s stays. All the qualitative and quantitative variables collected will be subject to a univariate descriptive analysis. First, the variables will be described (range, interquartile range, frequency, number, mean, median, standard deviation) and compared between the intervention and control arms to ensure that there is no imbalance between them. Comparability of arms will be tested using the Rao-Scott chi-square test for qualitative variables and the Wilcoxon non-parametric test for quantitative variables to take into account the hierarchical structure of the data (multiple stays in the same ward). The power of the study as well as within-period and between-period ICC values will also be calculated.

We will then conduct multivariate analyses to model the effect of the intervention on the adverse event rate by adjusting for the arm (control, passive and active feedback), the period (before and during intervention), and arm-period interaction. We will also consider the different identified predictors or potential confounding factors. A mixed effects logistic regression model will be developed using the NLMIXED procedure to take into account the two-level hierarchical structure of the data (“stay” level nested within a “ward” level). This type of model will make it possible to measure the degree of similarity between patients of the same cluster and the variability of the endpoint between clusters. A generalised estimation equation (GEE) model approach will also be tested if relevant using the GENMOD procedure. Quantitative variables will be considered in their continuous form, except if the assumption of linearity with the endpoint studied was not verified. Possible interactions will also be sought and taken into account in the model.

All confidence intervals will be calculated at 95%, and statistical test results will be presented at the 5% threshold. Tests will be bilateral and based on non-parametric statistics if necessary. All analyses will be performed using SAS software (SAS Institute Inc., Cary, NC, USA).

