#### Minimal effect demonstrable

Following the methodology introduced by Preisser et al. [26], we estimated the minimal demonstrable effect at a 44% reduction of adverse events in the intervention arms versus the control arm.

This estimation was based on the following assumptions: a baseline major adverse events rate of 10% for both control and intervention arms [27, 28], a post-intervention AE rate stable at 10% in the control arm, alpha risk at 5%, power at 80%, within-time ICC and between-time ICC at 0.026 and 0.022 respectively, a mean 2500 stays per ward and per year, and finally at least 40,000 stays per period (13,333 stays per arm and per period, accounting for about 5 wards).

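### The Wilcoxon test named for quantitative baseline variables does not account for stays clustered in wards, although the plan says it does

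*Protocol article*

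**What the plan says.** In the protocol article, section Data analysis, baseline variables are first described and then "compared between the intervention and control arms to ensure that there is no imbalance between them". The section names two tests. For the first, "Comparability of arms will be tested using the Rao-Scott chi-square test for qualitative variables". The second is "the Wilcoxon non-parametric test for quantitative variables to take into account the hierarchical structure of the data", and a parenthesis explains the structure meant: several stays in one ward. No clustered version of the Wilcoxon test is named, and no analysis of ward summaries.

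On the level and direction of testing, the same section says that "statistical test results will be presented at the 5% threshold" and that "Tests will be bilateral and based on non-parametric statistics if necessary".

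The outcome model comes next. It is a mixed logistic regression with stays nested in wards, containing arm, period and their interaction. On covariates the section says: "We will also consider the different identified predictors or potential confounding factors". It gives no rule for choosing them.

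**The concern.** A non-parametric test relaxes the assumption about the shape of the distribution. It does not relax independence. The ordinary rank-sum test computes its null variance as if each stay had been allocated to an arm on its own, whereas here the ward is allocated. The Rao-Scott test corrects its statistic for clustering; the rank-sum test has no such step. So the sentence gives the Wilcoxon test a property it lacks.

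The size of the wards makes this serious. With thousands of stays per ward, a small share of variance between wards is enough to make a stay-level test reject very often under correct randomisation. One baseline table would then judge its qualitative rows by a cluster-adjusted standard and its quantitative rows by an unadjusted one. A reader of that table could not tell a chance difference between a few wards from a notable imbalance.

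**Working it through.** **Inputs from the article.** Study design: wards randomised 1:1:1, stratified by centre. Minimal effect demonstrable: a mean of 2,500 stays per ward per year; 13,333 stays per arm per period, about 5 wards; "within-time ICC and between-time ICC at 0.026 and 0.022 respectively"; "alpha risk at 5%, power at 80"%; adverse event rate of 10% at baseline, staying at 10% in the control arm. No ICC is given for any quantitative baseline variable, so that is an assumption below.

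**The plan's own figure first.** The article states a minimal demonstrable reduction of 44%. I used a difference-in-difference on the logit scale, with a two-sided z test, 5 wards per arm and m = 2,500 per ward per period.

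- Design effect = 1 + (m − 1) × ICC = 1 + 2,499 × 0.026 = 65.97.
- Rates: p1 = 0.10, so p1q1 = 0.09; p2 = 0.10 × (1 − 0.44) = 0.056, so p2q2 = 0.0529.
- Intervention arm variance = [65.97/(2,500 × 0.09) + 65.97/(2,500 × 0.0529) − 2 × 0.022/√(0.09 × 0.0529)]/5 = (0.293 + 0.499 − 0.638)/5 = 0.0309.
- Control arm variance = [2 × 0.293 − 2 × 0.022/0.09]/5 = (0.586 − 0.489)/5 = 0.0195.
- Standard error = √(0.0309 + 0.0195) = 0.2245. Effect = logit(0.10) − logit(0.056) = 0.628.
- 0.628/0.2245 = 2.79, and power = Φ(2.79 − 1.96), about 79.8%. The reduction that gives exactly 80% is 44.1%.

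The figure reproduces, so the ward size and ICCs are being read as the plan uses them.

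**False-positive rate of a stay-level two-arm Wilcoxon test.** With no arm effect, clustering multiplies the variance of the statistic by about the design effect D, and the test ignores this. The true rejection rate is then 2 × [1 − Φ(1.96/√D)].

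At ICC 0.026: D = 65.97, √D = 8.12, 1.96/8.12 = 0.241, and the rate is 2 × [1 − Φ(0.241)] = 80.9%.

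| Assumed ICC of the baseline variable | D (m = 2,500) | Rate by formula | Rate by simulation |
|---|---|---|---|
| 0 | 1.0 | 5.0% | 5.0% |
| 0.001 | 3.5 | 29.5% | 27.5% |
| 0.005 | 13.5 | 59.4% | 58.9% |
| 0.01 | 26.0 | 70.1% | 71.2% |
| 0.026 | 66.0 | 80.9% | 81.0% |
| 0.05 | 126.0 | 86.1% | 86.5% |
| 0.10 | 250.9 | 90.2% | 90.6% |

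The simulation drew 5 wards of 2,500 stays per arm with no arm effect and applied the ordinary Mann-Whitney test, 1,000 runs per ICC. Using 13,333/5 = 2,667 stays per ward instead, ICC 0.026 gives 81.5%.

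**Allowance for stratification and specialty balance.** If these removed part of the between-ward variance, the residual ICC would be 0.026 × (1 − share removed):

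- 50% removed: ICC 0.013, rate about 73.5%.
- 80% removed: ICC 0.0052, rate about 60%.
- 90% removed: ICC 0.0026, rate about 47%.

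**The case against.** The strongest reply is that the purpose clause covers both tests and shows that the authors wanted a cluster-aware comparison. Clustered rank-sum tests exist, and a condensed article may have named one loosely. This is possible, and it is why the fix allows for it. But the sentence as it stands names the Wilcoxon test without qualification, and a reader or programmer would run the ordinary one. This is a wrong stated property, not a detail left to another document.

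The second reply concerns size. A reader might infer that about 80% of quantitative variables will be flagged. The article does not support that flat statement: 0.026 is its assumption for the adverse event rate. The formula also treats wards as simply randomised, while the article stratifies by centre and draws 15 wards from five unit types, and the figure showing which ward is in which arm is not available here. This reply stands, and the rate must be given as conditional. It does not rescue the test: the lowest ICC in the table still gives about six times the nominal rate.

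Third, a reader might object that the Wilcoxon test compares two samples while the trial has three arms. The text speaks of intervention arms against control, and the abstract compares each feedback arm with the standard arm. Pairwise comparisons fit that, so I make no point of it.

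Fourth, a reader might infer that false alarms will drive the choice of covariates or be taken as failed randomisation. The article says neither. It leaves the choice of covariates open, so such use is possible but not planned.

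Finally, the effect is judged by the arm-by-period interaction in a model with a ward level. The Wilcoxon p-values enter neither that estimate nor its test. This stands and limits the point.

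**Conclusion.** The point holds in a limited form. The article credits the Wilcoxon test with handling clustering, and the ordinary rank-sum test does not. With 5 wards per arm and 2,500 stays per ward, a two-arm stay-level comparison would flag a chance difference about 81% of the time at an ICC of 0.026, and about 30% to 90% of the time over ICCs of 0.001 to 0.10. These figures rest on three assumptions: that the ordinary test is meant, that baseline variables have ICCs in that range, and that neither stratification nor specialty balance removes much between-ward variance. The conclusion that the rate is far above 5% does not depend on the exact ICC.

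The direct damage is confined to the comparability check for quantitative variables, which cannot show what it is meant to show. It would be wrong to conclude from this that the trial's main result is invalid. It is a clear error outside the main effect test, and it should be corrected.

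**What to change.** In Data analysis, replace the Wilcoxon test with one of the following:

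- a clustered rank-sum test, in a version for whole clusters allocated to arms (if that was already meant, say so and name it); or
- a comparison between arms of ward-level means or medians.

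With 5 wards per arm the second is the simpler choice. An exact rank-sum test of 5 against 5 wards has 10!/(5! × 5!) = 252 arrangements, so its smallest two-sided p-value is 2/252 = 0.008 and a 5% test is possible. Power will be low with so few wards, so a non-significant result should not be read as proof of balance.

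Add that adjustment covariates will not be chosen from unadjusted stay-level p-values. Dropping baseline tests and describing balance by standardised differences would also remove the problem, but that is a reporting preference and not required.

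The cost is one or two sentences and minor programming. Data collection, sample size and the outcome model do not change.

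### The main model commits to no ward-by-period variation, although the sample size assumes it; with a ward intercept alone the arm-by-period test would run at about 56–62% type I error under the planning ICCs

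*Protocol article*

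**What the plan says.** In the protocol article, the section Minimal effect demonstrable plans on two correlations, "within-time ICC and between-time ICC at 0.026 and 0.022 respectively", with a mean of 2,500 stays per ward and year, about five wards per arm and a 10% event rate. From these it states: "we estimated the minimal demonstrable effect at a 44% reduction of adverse events in the intervention arms versus the control arm".

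The Data analysis section tests the intervention through the arm-by-period interaction. The model is given as "A mixed effects logistic regression model will be developed using the NLMIXED procedure to take into account the two-level hierarchical structure of the data", and the two levels are named as stay and ward. A GEE is an additional option, to be used if relevant. The same section says: "The power of the study as well as within-period and between-period ICC values will also be calculated". It does not say that those ICCs enter the model, and it names no reference distribution for the interaction test.

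**The concern.** A between-time ICC below the within-time ICC means that two stays in the same ward resemble each other less when they fall in different periods. The gap, 0.026 − 0.022 = 0.004, is a ward-by-period variance component: each ward's rate moves between periods for reasons unrelated to arm. At a 10% rate its SD is √(0.004 × 0.09) = 0.019, or 1.9 percentage points per ward and period.

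A ward random intercept is shared by both periods and drops out of the before–after change. If it is the only random effect, the model attributes all remaining variation in that change to binomial sampling of thousands of stays, which is small. Ordinary ward drift, averaged over only five wards per arm, can then pass for an intervention effect. The arm-by-period term is the answer to the trial's question, and a significant result is also what prompts the one-year follow-up measurement.

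**Working it through.** **Inputs** (protocol article). Within-time ICC ρw = 0.026, between-time ICC ρb = 0.022, 2,500 stays per ward-year, 5 wards per arm, 10% rate at baseline and in the control arm later, 80% power, 5% alpha (Minimal effect demonstrable); two-sided tests (Data analysis); about 40,000 stays before and 80,000 during the intervention (Number of subjects expected), which over 15 wards is 2,667 and 5,333 per ward.

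**1. Reproducing the 44%.** On the logit scale, the variance of an arm's mean change is (V0 + V1 − 2C)/5, with V = [1 + (m − 1)ρw]/[m p(1 − p)] and C = ρb/√[p0(1 − p0) p1(1 − p1)]. Take m = 2,500 in both periods and a fall from 10% to 5.6%.
- Control arm: V0 = V1 = 0.2932, C = 0.2444, variance = 0.0976/5 = 0.0195.
- Intervention arm: V0 = 0.2932, V1 = 0.4992, C = 0.3189, variance = 0.1545/5 = 0.0309.
- SE of the contrast = √0.0504 = 0.2245. Effect = logit(0.10) − logit(0.056) = −2.197 + 2.825 = 0.6275. Ratio = 2.795, so power = Φ(2.795 − 1.96) = 79.8%.

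Solving for 80% power gives 44.1% (43.6% with 5,000 stays in the second period). The stated figure is reproduced. With both ICCs at 0.026 the same formula gives 13–15%, so the 44% depends on the gap. (On the risk-difference scale the calculation gives about 49%, so the logit scale appears to be the one used.)

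**2. Variance with and without ward drift.** Under no effect, the variance of one ward's change divided by p(1 − p) is:
- planning ICCs: [1 + (n0 − 1)ρw]/n0 + [1 + (n1 − 1)ρw]/n1 − 2ρb
- ward intercept only: (1 − ρw)(1/n0 + 1/n1)

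The factor 2/5 that turns this into an arm contrast cancels from the ratio R of the first to the second. Type I error = 2[1 − Φ(1.96/√R)].

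| Stays before / during | Planning ICCs | Ward intercept only | R | √R | Type I error |
|---|---|---|---|---|---|
| 2,500 / 2,500 | 0.008779 | 0.000779 | 11.27 | 3.36 | 56% |
| 2,500 / 5,000 | 0.008584 | 0.000584 | 14.69 | 3.83 | 61% |
| 2,667 / 5,333 | 0.008548 | 0.000548 | 15.60 | 3.95 | 62% |

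In each row, 2 × 0.004 = 0.008 of the first variance is ward drift. A 14-df t cutoff (2.145) in place of 1.96 gives 52–59%: the standard error is wrong, not just the cutoff. Simulated trials with 15 wards and a ward-intercept logistic model gave 57–60% (2,500/2,500) and 59–63% (2,500/5,000), in agreement.

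**3. Sensitivity to the between-time ICC** (range over the three rows above).

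| ρb | Type I error |
|---|---|
| 0.022 | 56–62% |
| 0.024 | 43–50% |
| 0.025 | 30–36% |
| 0.026 | 5% |

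**4. Alternatives, simulated under no effect with 15 wards.**

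| Analysis | Type I error per contrast |
|---|---|
| GEE, ward-clustered robust SE, z test | about 12–15% |
| Ward plus ward-by-period random effects, Wald z | 9–11% |
| The same, t on 12 df | 6–8% |
| t test on ward-level changes in log-odds | 4.8–5.2% |

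The two mixed-model rows rest on 150 simulated trials per setting (300 contrasts), so 6–8% carries a Monte Carlo SE of about √(0.07 × 0.93/300) = 1.5 points.

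**5. Cost in power.** With t critical values in step 1, power at a 44% reduction is 69–70% on 8 df and 73–74% on 12 df. The reduction detectable with 80% power is 49–50% and 47–48% respectively.

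**The case against.** The strongest reply is that the article does not list the random effects. Two-level describes the data, and a ward intercept plus a ward-specific random period coefficient is still two-level; with two periods it contains all the ward-by-period variance. The team also means to estimate both ICCs, which requires separating that variance, and it keeps a GEE in reserve. A fuller analysis plan could settle the matter.

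Much of this stands. A reader might infer that the plan fixes an intercept-only model and that the trial's type I error therefore is 56–62%. The document does not support that: the figure is conditional on the intercept-only fit and on planning ICCs that the data may not bear out. The rows with a longer second period also assume that a two-year period has the same within-period ICC as one year. And the GEE, with ward-clustered robust errors, would remove most of the inflation.

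It does not dispose of the point. Nothing commits to the random period coefficient, the calculated ICCs are tied to no model, and the GEE is optional and still too liberal with 15 wards under a z test. The general remark that interactions will be explored does not promise a ward-by-period random effect. The model as described is at odds with the plan's own sizing assumption, which is more than a detail left for later.

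**Conclusion.** The point holds in conditional form. The sizing assumes ward-by-period variation, and the main model as described commits to no term that carries it. With a ward intercept alone and the planning ICCs, standard errors for the arm-by-period contrasts are 3.4–4.0 times too small and the type I error per contrast is about 56–62%. The size depends on the between-time ICC, but the error is still 30–36% when that ICC is only 0.001 below the within-time value, and it reaches 5% only with no ward drift, which the sizing itself does not assume. The 44% figure is not in error as a normal-approximation calculation; what conflicts with it is the model that is to deliver the test.

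**What to change.** Before the arms are unblinded, name one primary test of the arm-by-period term. The safer choice is an analysis of the 15 ward-level before–after changes in log-odds, either by a t test on about 12 df (fewer if centre strata are included) or by a permutation test that respects the stratification by centre. The t test held about 5% in simulation.

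The alternative is to keep the mixed model, add a ward-by-period random effect (or a ward-specific random period coefficient), and state small-sample degrees of freedom. This is not equivalent: it ran at about 6–8%. If the GEE is kept, it should be a sensitivity analysis with ward-clustered errors and a small-sample correction.

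No new data are needed. The cost is wider confidence intervals than an intercept-only model would report, and a power statement that has to change: with 8–12 df, about 69–74% at a 44% reduction. The minimal demonstrable effect should be restated as about a 47–50% reduction.

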**Methods:**

A cluster randomised controlled study will be performed at four study sites. The unit of randomisation is wards within the study sites. Fifteen wards will be randomly assigned to passive feedback, active feedback, or a standard MMC (control arm). Passive feedback and active feedback arms will be compared to standard arm in terms of occurrence of adverse events. The trigger tool methodology used to identify adverse events is a retrospective review of inpatient records using “triggers”: an adverse event is defined as a patient’s stay with at least one positive trigger.

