### Study design

A cluster randomised controlled study constituted by three arms will be conducted. The cluster units will be wards in the participating hospitals. After agreement to participate by the medical head of the wards, the wards will be randomly assigned to passive feedback, active feedback, or standard MMC (control arm) based on computer-generated randomisation sequence with a 1:1:1 treatment allocation ratio, stratified by centre. For methodological reasons, wards of the same specialty will belong to different hospitals in order to reduce the risk of contamination. The planned duration of the intervention is 2 years. Data will be collected at three points of assessment: (1) during 1 year prior to the intervention (pre-measurement), (2) for 2 years, starting 6 months after the start of the procedure, and (3) during 1 year after the end of the intervention (follow-up measurement) in case of significant results. Adverse event rates will be compared between arms before and during the intervention following a difference-in-difference analysis. Figure 1 illustrates the study process.

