### Study setting and recruitment

The Lyon University Hospital Federation (*Hospices Civils de Lyon* [HCL]) is a federation of academic healthcare organisations. The study concerns 15 wards among 4 hospitals (3 multidisciplinary and 1 specialised) located in Lyon (France). Figure 2 provides an overview over the submodules.

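### The arm-by-period model is assigned to NLMIXED with 15 wards and no named ward-by-period effect; even with that effect added, maximum likelihood makes the 5% test run at about 8% to 10.5%

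*Protocol article*

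**What the plan says.** In the protocol article, Data analysis, the fixed effects of the main model are "the arm (control, passive and active feedback), the period (before and during intervention), and arm-period interaction". The procedure is named: "A mixed effects logistic regression model will be developed using the NLMIXED procedure". The random structure is described as a "two-level hierarchical structure of the data (“stay” level nested within a “ward” level". No ward-by-period term is mentioned. A second model is conditional: "A generalised estimation equation (GEE) model approach will also be tested if relevant using the GENMOD procedure". Tests are two-sided at 5%, with 95% intervals.

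Under Study setting and recruitment, "The study concerns 15 wards among 4 hospitals". Under Study design, allocation is "1:1:1 treatment allocation ratio, stratified by centre", so about 5 wards per arm.

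Under Sample size, the 44% minimal demonstrable effect uses a within-time ICC of 0.026 and a between-time ICC of 0.022. Data analysis adds that "within-period and between-period ICC values will also be calculated".

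**The concern.** The arm-by-period contrast compares changes in ward rates between arms, so its information comes from 15 ward-level changes, however many stays each ward contributes. Two things have to be right: the model must let wards change by different amounts, and the variance of those changes must be estimated with allowance for the few wards.

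The text secures neither. Two different ICCs mean that a ward's rate drifts between periods beyond binomial noise, yet the model description has only stays within wards. The named procedure maximises the ordinary likelihood, which takes no account of the degrees of freedom used by the fixed effects. That is a known property of the software; the article does not state it. At stake are the stated 5% threshold and 95% intervals for both feedback arms.

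**Working it through.** **Inputs.** From the article: 15 wards, 5 per arm; 2,500 stays per ward per year; one year before and two years during; rate 10%; ICCs 0.026 and 0.022; two-sided 5%; power 80%; effect 44% (10% to 5.6%). Assumed: equal ward sizes, no ward-level covariates, logit scale.

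**1. The article's own figure.** With p(1−p) = 0.09 at 10% and 0.0529 at 5.6%, the variance of one ward's mean is (1 + 2499 × 0.026)/2500 = 0.02639 times p(1−p).
- Variance of a logit change, control ward: 2 × (0.02639 − 0.022)/0.09 = 0.0975.
- Intervention ward: 0.02639/0.09 + 0.02639/0.0529 − 2 × 0.022/√(0.09 × 0.0529) = 0.1545.
- SE of the contrast: √((0.0975 + 0.1545)/5) = 0.2245.
- Effect: ln(0.1/0.9) − ln(0.056/0.944) = 0.6275 in absolute size. Ratio: 2.795.
- Power with a normal reference: Φ(2.795 − 1.96) = 79.8% (80.7% with 5,000 stays in the intervention period).

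The 44% is therefore reproduced, on the logit scale and with normal quantiles. On the identity scale, power at 44% would be 71%.

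**2. Literal reading: ward intercept only.** The model attributes only binomial noise to a ward's change.
- 2,500 stays in each period: assumed variance (1/2500 + 1/2500)/0.09 = 0.0089. True variance adds 2 × (0.026 − 0.022)/0.09 = 0.0889, giving 0.0978. Ratio 11.0.
- 2,500 and 5,000 stays: 0.0067 against 0.0956. Ratio 14.3.
- Size = 2 × [1 − Φ(c/√ratio)]. With the first ratio this is 52% (c from t on 14 df) or 55% (normal). With the second it is 57% or 60%.
- In 3,000 simulated null trials with 2,500 and 5,000 stays, fitted by Laplace maximum likelihood, the size was 60% (t on 14 df) and 63% (normal).

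**3. Ward-by-period effect included, maximum likelihood.** Fifteen changes with three arm-specific means leave 12 df. Maximum likelihood divides by 15, so the expected variance ratio is 12/15 = 0.80 and the SE ratio √0.80 = 0.894. Size = P(|t12| > c × 0.894):

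| Reference | c | c × 0.894 | Size | Coverage |
|---|---|---|---|---|
| t, 13 df | 2.160 | 1.932 | 7.7% | 92.3% |
| t, 14 df | 2.145 | 1.918 | 7.9% | 92.1% |
| Normal | 1.960 | 1.753 | 10.5% | 89.5% |

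The same simulation, with the effect in the model, gave 8.5%, 8.6% and 10.6%; the estimated ward-by-period component averaged 0.78 of its true value. An unbiased variance with t on 12 df gives 5.0%.

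The factor 0.80 applies to the total variance of the ward changes. Binomial noise is not estimated, so the whole shortfall falls on the ward-by-period component: 0.20 × 0.0978/0.0889 = 22% (21.5% with 5,000 stays).

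**4. Interval width.** 0.894 × 2.160/2.179 = 0.887, so correct intervals are 1/0.887 = 1.13 times as wide as under maximum likelihood with t on 13 df.

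**5. Power with 12 df.** Noncentral t with noncentrality 2.795 and critical value 2.179: about 73% at the 44% effect.

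**The case against.** **The 8% is not the error of the model as written.** A reader might take 8%, with 92% coverage, as the operating characteristic of the plan. The text does not support that. It names no ward-by-period effect, and on the literal reading the omission dominates. The 8% is what remains after that is repaired.

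**Nor is the 50% to 60% certain.** A random period effect at ward level could still be called two-level, and both ICCs are to be calculated. But calculating them does not put the term in the main model. On neither reading does the test run at 5%.

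**The reference distribution is unstated.** This stands. The 13 or 14 df are assumptions about the software default, hence the range from about 8% to 10.5%. Degrees of freedom are commonly left to an analysis plan that is not shown, so their absence is no finding. The finding is the named procedure.

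**NLMIXED is not irreparable.** It accepts user-set degrees of freedom. By the formula above, 6 df with the maximum likelihood SE would give 4.9%. It would be too strong to say that nothing within the procedure can correct the size.

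**GEE is also foreseen.** True, so the analysis is not confined to NLMIXED. But GEE is conditional, and with 15 wards it does not by itself cure the small-sample problem.

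**Two comparisons.** The chance of at least one false positive is about 13.5% under maximum likelihood with t on 13 df. A correct 12-df test already gives about 8.9%, so only some 5 points come from the estimator.

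**Conclusion.** The concern holds in two parts. The model description, read literally, contradicts the ICCs behind the sample size and would give an error of roughly 50% to 60%. With a ward-by-period effect added, the named procedure still understates the variance of the ward changes by about 20%. Size per comparison is then about 8% (t on 13 or 14 df) to 10.5% (normal), and coverage about 92% to 89.5%.

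These figures rest on equal ward sizes, no ward-level covariates, the article's ICCs, and the stated property of NLMIXED. Fitting centre or ward-level covariates would leave fewer than 12 df and worsen the maximum likelihood figures.

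**What to change.** In Data analysis, state ward and ward-by-period random effects and a small-sample method. Either of these would serve:
- GLIMMIX with restricted pseudo-likelihood (RSPL) and Kenward-Roger degrees of freedom, which stays within SAS.
- A t-test on the 15 ward-level changes in log-odds with about 12 df, fewer if centre or ward-level covariates are fitted.

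Optionally, confirm the p-values with a permutation test that follows the centre-stratified randomisation.

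**Cost.** A change of procedure and a sentence or two of text. Intervals are about 13% wider than under maximum likelihood with t on 13 df. Power at 44% is about 73% instead of the stated 80%, so the minimal demonstrable effect under Sample size should be restated on the same basis. By the formula in step 1, a 48% reduction (10% to 5.2%) has effect 0.706, SE 0.2304 and ratio 3.06, which gives about 80% power with t on 12 df.

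### If the optional GEE in GENMOD is reported with the usual Wald inference, 15 wards are too few: about 12–14% type I error per comparison instead of 5%, and intervals too narrow

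*Protocol article*

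**What the plan says.** The Data analysis section of the protocol article first names a mixed effects logistic model fitted in NLMIXED, with stays nested in wards and terms for arm, period and their interaction. It then adds: "A generalised estimation equation (GEE) model approach will also be tested if relevant using the GENMOD procedure". It does not say when the GEE becomes relevant or what role it has beside the mixed model. It also gives no variance estimator, small-sample correction, reference distribution or type of test for it. Confidence intervals are at 95% and tests at 5%; "Tests will be bilateral and based on non-parametric statistics if necessary".

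On the number of clusters, the abstract says "Fifteen wards will be randomly assigned to passive feedback, active feedback, or a standard MMC (control arm", and Study design says the wards are allocated "with a 1:1:1 treatment allocation ratio, stratified by centre". The section on the minimal demonstrable effect gives "13,333 stays per arm and per period, accounting for about 5 wards".

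**The concern.** The empirical sandwich variance of a GEE is justified by a large number of clusters, not a large number of stays. With about 5 wards per arm it has two faults. It is biased low, because residuals are taken around means estimated from the same few wards. It is also itself poorly estimated, so a normal quantile is too small. The roughly 120,000 expected stays (40,000 before and 80,000 during the intervention) cure neither fault.

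At stake is the arm-by-period contrast, which is the trial's main question. If the GEE were reported with ordinary Wald inference, its intervals would look more precise than the design allows, and a chance difference between wards could be read as an effect of feedback. Because the article gives no criterion for using the GEE, its result could appear beside or in place of that of the mixed model.

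**Working it through.** **Inputs, all from the protocol article**
- 15 wards at 1:1:1, so k = 5 per arm (abstract, Study design).
- "a baseline major adverse events rate of 10% for both control and intervention arms"; "a post-intervention AE rate stable at 10% in the control arm".
- Within-period ICC 0.026 and between-period ICC 0.022; mean 2,500 stays per ward-year; "alpha risk at 5%, power at 80"%; stated minimal effect a 44% reduction (Minimal effect demonstrable).
- One year before against two years of intervention (Data analysis), so 2,500 stays per ward before, and 2,500 or 5,000 during.

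**Step 1. The plan's own figure.** On the logit scale, the variance of one arm's change is

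(1/k) × [ (1+(m1−1)ρw)/(m1·p1·q1) + (1+(m2−1)ρw)/(m2·p2·q2) − 2ρb/√(p1·q1·p2·q2) ].

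With m1 = m2 = 2,500:
- Control arm (10% to 10%): (0.2932 + 0.2932 − 0.4889)/5 = 0.0195.
- Intervention arm (10% to 5.6%): (0.2932 + 0.4992 − 0.6379)/5 = 0.0309.
- Standard error: √(0.0195 + 0.0309) = 0.2245.
- Effect: logit(0.10) − logit(0.056) = 0.6275, which is 2.795 standard errors.
- Power with normal quantiles: Φ(2.795 − 1.96) = 79.8%.

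Solving for 80% power gives a 44.1% reduction, or 43.6% with 5,000 intervention-period stays. The stated figure therefore reproduces with normal quantiles, that is, without allowance for the small number of wards. With t quantiles on 8 degrees of freedom it would be 50.0%. Some other combinations of scale and quantile also come close to 44%, so the match is consistent with a normal reference but does not prove one.

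**Step 2. Closed form for the Wald test.** Take equal wards and let d be each ward's change on the logit scale. The uncorrected sandwich estimates the variance of an arm's mean change by Σ(d − mean)²/k². Its expectation is (k−1)/k = 4/5 of the true variance. A pairwise contrast uses two arms, so 2 × (5−1) = 8 degrees of freedom. The Wald z test rejects when |t8| > 1.96 × √0.8 = 1.753, which has probability **11.8%**. Removing only the bias and keeping the normal quantile still leaves P(|t8| > 1.96) = 8.6%.

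Interval width: 1.96 × √0.8 / 2.306 = 0.76, so the interval is about 24% shorter than the matching t interval.

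**Step 3. Simulation.** 20,000 null trials per setting: 15 wards, 10% rate, the stated ICCs, arm × period logit model, independence GEE, uncorrected sandwich, normal reference, one comparison with control. Ward-size CV is an assumption, since the article gives only a mean.

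| Ward-size CV | Stays before/during | Type I error |
|---|---|---|
| 0 | 2,500/2,500 | 13.6% |
| 0 | 2,500/5,000 | 12.7% |
| 0.3 | 2,500/5,000 | 13.9% |
| 0.5 | 2,500/5,000 | 15.9% |
| 0.7 | 2,500/5,000 | 18.9% |

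With equal wards and 2,500/5,000 stays, at least one of the two comparisons with control is falsely significant in 22% of null trials.

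**Step 4. The same data with a correction.**
- Mancl-DeRouen variance with t on 8 degrees of freedom: 3.5% to 4.2% with equal wards, 5.2% at CV 0.7.
- Mancl-DeRouen variance with t on 12 degrees of freedom (15 wards minus 3 arms): 5.0% to 5.3% with equal wards.
- Mancl-DeRouen variance with the normal quantile: 6.6% to 7.2% with equal wards.
- Uncorrected variance with t on 8 degrees of freedom: 8.1% to 8.6% with equal wards.

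Both parts of the correction are needed.

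**The case against.** The strongest reply is that the article does not fix what is criticised. A reader might infer that the plan uses an uncorrected sandwich with a normal reference. The text names only a model and a procedure, and the rest is inferred from the procedure's usual output. A correction could be specified in an analysis plan that is not shown. This stands, and the point has to be conditional.

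The size also depends on the test. A generalised score test on the same design (balanced wards, normal approximation) gives 5.6% for a pairwise contrast and 2.9% for the joint test, so GEE with 15 wards does not in itself imply inflation. This stands too. It does not rescue the promised 95% intervals if those are built from uncorrected standard errors.

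A reader might further infer that about 13% is the error rate of the trial's main analysis. The documents do not support that: the mixed model comes first and the GEE is conditional on being relevant. Nor does the sample-size section show that a GEE is likely to lead. It cites a published methodology without naming GEE, and that source is not at hand.

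Finally, the calculations leave out stratification by centre and covariate adjustment, and the choice between 8 and 12 degrees of freedom is a judgement. This stands, but it does not alter the order of magnitude, which is set by the number of wards.

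**Conclusion.** The point holds in conditional form. A GEE in GENMOD reported with Wald tests from the empirical sandwich and a normal reference would have a type I error of about 12–14% per comparison at a nominal 5%. This rests on 5 equal wards per arm and the article's own rate and ICCs. Unequal wards make it worse, with about 16% at an assumed CV of 0.5. Emergency, intensive care, surgical and obstetric wards are unlikely to be of equal size, so the equal-ward figure is probably the favourable case. The result says nothing about the error rate of the mixed model, which is a separate question. It deserves action before the analysis because the named route gives intervals that are too narrow and a better one is readily available.

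**What to change.** If the GEE is kept, state that it will use a small-sample-corrected sandwich variance (for example Mancl-DeRouen) with a t reference on ward-level degrees of freedom, fixed in advance between 8 and 12. Eight is the more cautious choice. Run it through a SAS procedure or macro that offers the correction, and label the GEE as a sensitivity analysis to the mixed model.

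The drafting and programming cost is small: a sentence or two and a change of procedure or macro. The statistical cost should be acknowledged. Intervals widen, and apparent power falls. With t on 8 degrees of freedom, power at the stated 44% reduction is about 69% (70% with 5,000 intervention-period stays) instead of 80%, and the minimal demonstrable reduction rises from 44% to about 50%. That loss reflects the number of wards and is not created by the correction.
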